### D. 4. STATISTICAL CONSIDERATIONS

**Primary endpoints.** a) Incidence/Prevalence of BV at cross-sectional visits; b) Portion of pregnancies lost during the first 14 weeks of gestation; c) Incidence of adverse reactions to the product (portion of subjects having adverse reactions); and d) Rates of participation in study, adherence to treatment, and subsequent dropout.

**Sample size and power.** The following design specifications will apply: number of treatment groups: 2; follow-up period: approximately one year; hypotheses will be tested using a one-sided type 1 error of  $\alpha=0.05$ . Unless stated otherwise, powers are obtained based on Fisher's exact test for comparisons of proportions in two groups using software developed by Dupont and Plummer (56).

We will recruit 1664 women of whom 832 will be HIV infected and 832 will be uninfected. In each group of women, 416 will be randomized to treatment arm and 416 to placebo arm. Based on previous experience in Malawi, losses due to dropouts and non-compliance will be less than 10% per year. Thus at least 375 women in each arm will return to each study visit during the first year.

**Specific aim 1.** Power estimates for specific aim 1 is shown in Tables 11. In previous studies from Malawi, cross sectional prevalence of BV among untreated women was 30% and that of any vaginal disturbance was 89% (24).

**Table 11. Estimated power for specific aim 1 (comparing BV at each visit during the first study year assuming at least 375 evaluable study subjects in each group).**

| Normative rate
in untreated women | Reduction from intervention |            |
|----------------------------------------------|------------------------------------|------------|
|                                              | 33%                         | 50% |
| 0.30                                         | .87                                | ~1.00      |
| 0.89                                         | ~1.00                              | ~1.00      |

Thus there will be 0.87 and almost 1.00 power to detect 33% reductions in cross sectional visit prevalence of BV (normative rate 0.30 in untreated subjects) and any vaginal flora disturbance (normative rate .89 in untreated subjects).

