**Table 12. Estimated power for specific aim 2 assuming 300 evaluable subjects in each group during the first year.**

| Normative rate of
pregnancy loss | Reduction from intervention |            |
|---------------------------------------------|------------------------------------|------------|
|                                             | 33%                         | 50% |
| 0.20                                        | .54                                | .91        |
| 0.30                                        | .78                                | .99        |

**Data management.** Data entry and storage will be conducted on-site. The Johns Hopkins Project in Malawi has trained staff who have performed this activity for over a decade. Each record will be double entered into the computer and records compared. No direct subject identifiers (e.g., names, addresses, etc.) will be entered into data sets. The data will be stored on secure computers in Malawi and Johns Hopkins University. All original data collection forms will be kept in locked file cabinets. Data entry and management procedures are described further under Quality Control and Assurance (section D. 5). FoxPRO and SAS for windows are available for data management in Malawi. Computers used in the study are protected against computer virus attack by Norton antiviral software. All data sets are backed up onto tapes on a weekly basis both at Malawi and Johns Hopkins University (JHU). For this study we propose to manage the data locally in Malawi and perform further management and data analyses at JHU in Baltimore. The data will electronically be transferred to Baltimore.

**Data analysis.** Analyses will be done using an intention to treat approach. Separate analyses for HIV infected and uninfected women will be performed and the effect of the intervention on outcomes in these two groups will be compared. The effect of the intervention will be based on comparing incidence of BV and portion of pregnancy losses between treated and untreated (control) subjects.

Multiple hypotheses will be tested in this study, requiring a diverse array of analytical methods

 Although we use the term incidence in the text, it is more accurate to define this measure as cross-sectional prevalence because the number of BV cases during a 3 month interval are a combination of new and continuing cases (due to incomplete cure and recurrences).

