For some analyses we will pool repeated measurements from the same individual over multiple study visits. For example, occurrence of BV across all post-intervention study visits will be compared between study groups. For these analyses, generalized estimation equation models, which use an individual as cluster unit, will be fit to obtain robust covariance. For binary outcomes, a logit link will be used.

Data monitoring and reporting. This trial will be monitored by a Data and Safety Monitoring Board (DSMB). Formal interim analyses of efficacy of the intervention, based on the primary endpoints, will then be performed at approximately six month intervals during the projected study duration. Recommendations for early termination of positive or negative results will be guided by the symmetric group sequential O'Brien-Fleming Boundary (58). The O'Brien-Fleming design allows for early termination if extreme initial results are seen, while essentially allowing employment of the standard single stage one-sided 0.025-level test statistic at the final analysis if it is reached. This enables one to maintain the power of the single-stage design in the presence of interim monitoring without having to increase the maximum sample size. As has been the plan for other clinical trials conducted by our research team in Malawi, we will arrange for regular dissemination of information.

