#### 12.3.1 Instructions for using the allocation study ID's

##### By Whom

Study coordinator (as the rest of the study investigators and workers, the study coordinator is completely blinded about the treatment assignment).

Procedure

1. Assign these Lists to the five Study Clinics as shown in section 12.3. above
2. Each woman enrolling in the study will be sequentially assigned the next available ID in each clinic.

12.4 Sample size and analysis plan12.4.1 Sample size and power:

The following design specifications will apply: number of treatment groups: 2; follow-up period: approximately one year; hypotheses will be tested using a one-sided type 1 error of  $\alpha=0.05$ . Unless stated otherwise, powers are obtained based on Fisher's exact test for comparisons of proportions in two groups.

We will recruit 1664 women of whom 832 will be HIV infected and 832 will be uninfected. In each group of women, 416 will be randomized to treatment arm and 416 to placebo arm. Based on previous experience in Malawi, losses due to dropouts and non-compliance will be less than 10% per year. Thus at least 375 women in each arm will return to each study visit during the first year.

Primary endpoint: effect of treatment on BV incidence. Power estimates for this primary endpoint are shown in Tables 12.1. In previous studies from Malawi, cross sectional prevalence of BV among untreated women was 30% and that of any vaginal disturbance was 89%.

**Table 12.1. Estimated power for specific aim 1 (comparing BV at each visit during the first study year assuming at least 375 evaluable study subjects in each group).**

| Normative rate
in untreated women | Reduction from intervention |       |
|--------------------------------------|------------------------------------|-------|
|                                      | 33%                                | 50%   |
| 0.30                                 | .87                         | ~1.00 |
| 0.89                                 | ~1.00                       | ~1.00 |

Thus there will be **0.87** and almost **1.00** power to detect 33% reductions in cross sectional visit prevalence of BV (normative rate 0.30 in untreated subjects) and any vaginal flora disturbance (normative rate .89 in untreated subjects).

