### 12.6 Data analysis.

Analyses will be done using an intention to treat approach. Separate analyses for HIV infected and uninfected women will be performed and the effect of the intervention on outcomes in these two groups will be compared. The effect of the intervention will be based on comparing incidence of BV and portion of pregnancy losses between treated and untreated (control) subjects.

Multiple hypotheses will be tested in this study, requiring a diverse array of analytical methods to compare the treatment and control arms. Descriptive comparisons will be made between the two study groups to identify potential confounding variables which could bias hypothesis testing through direct comparisons. When possible, as differences are noted, multivariate adjustment methods will be used to minimize the effect of confounders on testing the hypotheses. Continuous variables will be tested for skewness, kurtosis and outliers which could cause imprecision in standard asymptotic statistical methods. When such conditions occur, transformations such as logarithms, dichotomization or Winsorizing will be used, or nonparametric statistical methods will be implemented. For the statistical tests described below, both P-values and confidence intervals will be calculated for the parameters of interest.

---

 Although we use the term incidence in the text, it is more accurate to define this measure as cross-sectional prevalence because the number of BV cases during a 3 month interval are a combination of new and continuing cases (due to incomplete cure and recurrences).

Most outcomes of interest (e.g., presence of BV) are uncensored binary or categorical events. These include demographic and specific behavioral factors, etc. Contingency (n x 2) tables will be used to compare these events between the two study arms. Adjustment for covariates will be made with logistic regression. Comparison of binary events between two time-points within the same group will be done using methods that match on the same individual such as discordant pairs or conditional logistic regression. In other outcomes of interest which are continuous comparison of mean values will be made using t-tests. Adjustments for covariates will be performed through linear regressions. Comparisons of continuous covariates for the same individuals in a group over different time periods will be made using paired z-tests and linear regressions on differences of values.

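### Non-compliance is subtracted from the sample size although the analysis is intention to treat, so the power inputs do not match the planned analysis; the effect on power is a few points and depends on unstated assumptions

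*Protocol*

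**What the plan says.** The research plan (D.4, Sample size and power) and the manual of operations (12.4.1) carry the same text. In each HIV stratum, "416 will be randomized to treatment arm and 416 to placebo arm". The allowance is that "losses due to dropouts and non-compliance will be less than 10% per year", and the next sentence concludes: "Thus at least 375 women in each arm will return to each study visit during the first year". Tables 11 and 12.1 give power with 375 per arm, including .87 for a 33% reduction from a BV prevalence of 0.30. Table 12 is headed "Estimated power for specific aim 2 assuming 300 evaluable subjects in each group during the first year"; the 300 is 80% of 375, the share assumed to become pregnant again.

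On method, the "powers are obtained based on Fisher's exact test for comparisons of proportions in two groups", and "hypotheses will be tested using a one-sided type 1 error of" 0.05. The data monitoring paragraph of D.4 instead describes the "standard single stage one-sided 0.025-level test statistic at the final analysis".

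On the analysis set, D.4 (Data analysis) and 12.6 agree: "Analyses will be done using an intention to treat approach".

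Both sets of power tables describe the effect only as a percentage reduction due to the intervention. Neither says whether that is the effect in women who use every course or the effect as randomised.

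**The concern.** Dropout and non-compliance act differently under intention to treat. A woman who drops out gives no outcome at later visits, so she reduces n. A woman who returns but has not used the gel gives an outcome and is counted in her randomised arm, so she reduces the difference between arms. The plan puts both into one figure and applies it to n alone. It then infers from dropout and non-compliance together how many women will come back, although not using the gel does not decide who returns.

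The plan itself allows for gel non-use. Adherence is a listed endpoint (D.4 and 12.2.2). Under 3.2.3, a woman who misses V2 receives no tube for that course but continues to V3. Under 13.3, women who become pregnant stop the product and stay in follow-up. None of this enters the power calculation.

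At stake is how far the tables describe the power of the planned analysis. Power is usually more sensitive to a diluted effect than to the same percentage lost from n, so where the 10% is placed matters.

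**Working it through.** **Inputs from the plan.** 416 per arm in each HIV stratum; a combined allowance of 10% (stated as an upper bound, split not given); control BV rate 0.30; control pregnancy-loss rates 0.20 and 0.30; reductions of 33% and 50%; Fisher's exact test; intention to treat.

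**Assumptions added here, not in the plan.** The reductions are full-use effects, use is all or none, and non-users in the active arm keep the placebo rate.

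**Formulas.** With non-use proportion c and relative reduction r, the active-arm rate under intention to treat is p₂ = p₁ × [1 − r × (1 − c)]. The number analysed per arm is n = 416 × [1 − (0.10 − c)], because only the part of the 10% that is dropout leaves the sample. For Table 12, n is multiplied by 0.8. Power is the exact power of one-sided Fisher's test, enumerated over both binomial distributions.

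**Step 1: reproduce the printed figures.** 416 × 0.90 = 374.4, taken as 375, and 375 × 0.8 = 300. With 375 per arm and 0.30 vs 0.30 × 0.67 = 0.201, power is 0.865 at one-sided 0.025 (0.872 if the active rate is rounded to 0.20), which matches .87. At the declared one-sided 0.05 it is 0.921. Table 12 with 300 per arm shows the same pattern. At 0.025 the cells are 0.543, 0.920, 0.775 and 0.992, against printed .54, .91, .78 and .99. The tables were therefore computed at one-sided 0.025 (two-sided 0.05), not at the declared level.

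**Step 2: redistribute the stated 10% for BV, 33% reduction from 0.30.**

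- All 10% is non-use: n = 416, p₂ = 0.30 × (1 − 0.33 × 0.90) = 0.2109.
- 5% loss and 5% non-use: n = 416 × 0.95 = 395, p₂ = 0.30 × (1 − 0.33 × 0.95) = 0.2059.

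| Case | n per arm | Active rate | Power, one-sided 0.025 | Power, one-sided 0.05 |
|---|---|---|---|---|
| As in the plan | 375 | 0.201 | 0.865 | 0.921 |
| 5% loss, 5% non-use | 395 | 0.206 | 0.845 | 0.908 |
| All 10% non-use | 416 | 0.211 | 0.821 | 0.892 |

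For a 50% reduction from 0.30 with all 10% as non-use (0.30 vs 0.165, 416 per arm), power is still above 0.99 at 0.025. The 0.89 row stays at about 1.00.

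**Step 3: the same for Table 12, all 10% non-use.** n = 0.8 × 416 = 333 per arm.

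| Control rate, reduction | Printed | Diluted rate | Power, one-sided 0.025 | Power, one-sided 0.05 |
|---|---|---|---|---|
| 0.30, 33% | .78 | 0.211 | 0.73 | 0.82 |
| 0.20, 33% | .54 | 0.141 | 0.49 | 0.62 |
| 0.20, 50% | .91 | 0.110 | 0.88 | 0.93 |

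The .99 cell (0.30, 50%) becomes 0.98 at 0.025.

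**Step 4: the other meaning of the reductions.** If 33% is the effect as randomised, non-use is already inside it and p₂ stays at 0.201. Only dropout is then subtracted, so n lies between 375 (all of the 10% is dropout) and 416 (none is). BV power at 0.025 then runs from 0.865 to 0.898, and the printed .87 is at the low end.

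**The case against.** The strongest objection is that a reader might infer from the mismatch that the printed powers are simply too high, and the plan does not support this. At the alpha that it declares, one-sided 0.05, the diluted cases give 0.89 and 0.91 for BV against .87, and 0.82, 0.62 and 0.93 for Table 12 against .78, .54 and .91. All are above the printed values. This objection stands. The tables happen to be conservative at the declared level because they were computed at a stricter one.

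Secondly, a reader might take the 33% as an effect under full gel use. Nothing says so. Beside an intention-to-treat analysis, an as-randomised effect is a natural reading, and then no dilution is owed. This also stands, but it does not rescue the 375: on that reading non-compliant women should not be removed from 416 at all.

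Thirdly, the sentence on women returning to each visit suggests that non-compliance may mean missed visits. If so, the subtraction is right, and the open question is only whether the reductions already allow for gel non-use.

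Fourthly, one could reach a BV power of about .78 at 0.025 by taking 10% loss and a further 10% non-use (375 per arm, 0.30 vs 0.211). That exceeds the combined allowance of less than 10% in the plan, so it is not a figure the documents support.

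Finally, the plan reports confidence intervals with P-values, so a null result would not be judged on the planned power alone. This limits the consequence.

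**Conclusion.** The mismatch is real: one allowance covers two different things, it is applied only to n, and the analysis is intention to treat. The printed n and effect size fit that analysis only if all of the 10% is attendance loss and the reductions are as randomised, and the text establishes neither.

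The size is modest. If the reductions are full-use effects, non-users keep the placebo rate, and the 10% is only redistributed, BV power for a 33% reduction falls by about 2 to 4 points at one-sided 0.025 (0.865 to 0.845 or 0.821). With all 10% as non-use, the three Table 12 cells fall by about 3 to 5 points. The cells near 1.00 barely change. The direction is the same at one-sided 0.05, but from a higher start, so the results there stay above the printed values.

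An unqualified statement that the powers are overstated would therefore go too far. No single replacement figure can be adopted until the alpha and the meaning of the reductions are settled.

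**What to change.** In D.4 and 12.4.1:

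1. Replace the pooled allowance by two assumptions: loss to follow-up, which reduces n, and gel non-use, which reduces the effect.
2. Say whether the 33% and 50% reductions are full-use or as-randomised effects. If as randomised, subtract only dropout from 416.
3. Reconcile the declared one-sided 0.05 with the 0.025 behind the tables and in the D.4 monitoring paragraph.
4. Restate Tables 11/12.1 and 12/12.2 at that one alpha, as a range over the stated assumptions.

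The cost is one reworded paragraph and a few table cells in each section. Enrolment and the analysis stay as they are. Depending on the alpha chosen, the stated power may come out slightly lower or slightly higher than printed.

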¶ Women having either LBW, short gestational age (<37 weeks) or neonatal deaths.

**BV association with HIV infection.** Increasing severity of disturbance of vaginal flora was significantly associated with prevalent HIV infection (Table 6). This trend persisted after adjusting for concurrent STDs, sexual activity, and socioeconomic factors. As expected, STDs such as syphilis, gonorrhea and trichomoniasis were significantly associated with prevalent HIV infection (34). More importantly, in our longitudinal studies, BV was significantly associated with acquisition of HIV during pregnancy and postpartum. Among 1196 HIV seronegative women who were followed antenatally for a median of 3.4 months, 27 women seroconverted by time of delivery. Postnatally, 97 seroconversions occurred among 1169 seronegative women who were followed for a median of 2.5 years. BV was significantly associated with antenatal HIV seroconversion (adjusted odds ratio=3.7) and postnatal HIV seroconversion (adjusted rate ratio=2.3). There was a significant trend of increased risk of HIV seroconversion with increasing severity of vaginal disturbance among both antenatal and postnatal women. The approximate attributable risk of BV alone was 23% for antenatal HIV seroconversions and 14% for postnatal seroconversions (24). In addition to BV, this study showed that syphilis, gonorrhea and trichomoniasis were independently associated with HIV seroconversion.

**Table 6. Prevalence of HIV among pregnant women with disturbance of vaginal flora, 1990 and 1993 cohorts, Blantyre, Malawi.**

| Disturbance of vaginal flora | 1990 (N=6677) | 1993 (N=2449) |
|------------------------------|---------------|---------------|
| Overall                      | 22.5%         | 30.0%         |
| Normal                       | 10.1%         | 18.1%         |
| Mild                         | 17.0%         | 24.4%         |
| Moderate                     | 24.9%         | 33.5%         |
| Severe                       | 30.8%         | 43.9%         |
| P-value*                     | <0.0001       | <0.0001       |

\*  $X^2$  trend test.

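### The BV power tables apply one mixed-HIV control rate (0.30) to both HIV strata, although the protocol's own tables imply about 26% in HIV-uninfected and 42% in HIV-infected women; the printed .87 also rests on an alpha other than the one stated

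*Protocol*

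**What the plan says.** The power statement appears twice with the same figures: Research Plan D.4 (Table 11) and Manual of Operations 12.4.1 (Table 12.1).

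- **Size:** the target is 1664 women, split equally by HIV status (832 per stratum). On allocation the text reads "In each group of women, 416 will be randomized to treatment arm and 416 to placebo arm". Losses below 10% per year leave at least 375 per arm at each visit.
- **Control rate:** "cross sectional prevalence of BV among untreated women was 30" per cent. This is the only BV rate used, and it gives .87 for a 33% reduction.
- **Test and level:** "powers are obtained based on Fisher's exact test for comparisons of proportions in two groups", and "hypotheses will be tested using a one-sided type 1 error of" 0.05. D.4, under data monitoring, instead describes using the "standard single stage one-sided 0.025-level test statistic at the final analysis".
- **Analysis:** 12.6 says "Separate analyses for HIV infected and uninfected women will be performed", after which the effects in the two groups are compared. Sections 5.7 and 12.3 give each HIV group its own randomization list.
- **BV and HIV:** Section C.1 reports "Increasing severity of disturbance of vaginal flora was significantly associated with prevalent HIV infection (Table 6"), with P<0.0001 for trend in both cohorts.

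**The concern.** The sample size and the analysis are both set by HIV stratum, but the control rate is not. The 30% matches Table 3, a survey of 9126 pregnant women. Table 6 covers the same number of women (6677 + 2449 = 9126), about a quarter of them HIV infected, and shows HIV to be much more frequent among women with BV. If BV differs that much by HIV status, 30% describes neither half of a trial that enrols 832 women of each status. For a fixed relative reduction and fixed numbers, power depends on the control rate, so the two strata cannot share a figure.

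At stake is how each stratum's result on the leading primary endpoint is read. A reader told that both strata have .87 power will give a null result the same weight in either. Because the power section and the monitoring section name different significance levels, the reader also cannot tell what the .87 refers to.

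**Working it through.** **1. What the 375 counts.** 832 / 2 = 416 per arm within one HIV group; 416 × 0.9 = 374.4, printed as 375. Tables 11 and 12.1 therefore give power within one stratum at a single visit.

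**2. Reproducing the printed .87.** Exact power of Fisher's test, 375 per arm, 0.30 against 0.30 × 0.67 = 0.201:

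- one-sided 0.025: .865 (.872 if the reduction is exactly one third)
- one-sided 0.05: .921 (.926)

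Only 0.025 reproduces .87. Table 12 in D.4 (300 per group) points the same way:

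| Control rate, reduction | Printed | At 0.025 | At 0.05 |
|---|---|---|---|
| 0.20, 33% | .54 | .54 | .66 |
| 0.20, 50% | .91 | .92 | .96 |
| 0.30, 33% | .78 | .78 | .86 |
| 0.30, 50% | .99 | .99 | 1.00 |

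**3. BV rate by HIV status.** Inputs are BV 30.0% (Table 3); HIV prevalence overall of 22.5% (1990) and 30.0% (1993); and HIV prevalence among women with BV of 30.8% and 43.9% (Table 6). Table 3 is not split by year, so 30% in each year is an assumption.

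P(BV | HIV+) = P(BV) × P(HIV+ | BV) / P(HIV+), and likewise for HIV−.

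- 1990: HIV+ 0.30 × 0.308 / 0.225 = 41.1%; HIV− 0.30 × 0.692 / 0.775 = 26.8%
- 1993: HIV+ 0.30 × 0.439 / 0.300 = 43.9%; HIV− 0.30 × 0.561 / 0.700 = 24.0%
- Pooled counts: HIV+ = 0.225 × 6677 + 0.30 × 2449 = 2237. BV = 0.30 × 9126 = 2738. Both = 0.308 × 0.30 × 6677 + 0.439 × 0.30 × 2449 = 940.
- Pooled rates: HIV+ 940 / 2237 = 42.0%; HIV− (2738 − 940) / (9126 − 2237) = 26.1%

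Consistency check: weighting Table 6 by the Table 3 shares returns overall HIV prevalence of 22.1% and 31.5%, against the stated 22.5% and 30.0%.

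Sensitivity: with BV at 31% in 1990 and 27% in 1993, the pooled HIV+ rate is (0.308 × 0.31 × 6677 + 0.439 × 0.27 × 2449) / 2237 = 41.5%, and the pooled HIV− rate barely moves (26.2%). The 1993 HIV− rate taken alone moves more, to 0.27 × 0.561 / 0.70 = 21.6%.

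**4. Power by stratum.** 33% reduction, 375 per arm, Fisher's exact test; brackets give the range over the two cohort-specific rates.

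| Control rate | One-sided 0.025 | One-sided 0.05 |
|---|---|---|
| 0.30 (as planned) | .865 | .921 |
| HIV-uninfected, 0.261 | .794 (.75–.81) | .872 (.84–.88) |
| HIV-infected, 0.42 | .975 (.97–.98) | .989 (.99) |

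The gap between strata is 18 points at 0.025 and 12 points at 0.05.

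**The case against.** - **At the stated alpha, the HIV-uninfected power is .87.** This stands as arithmetic. A reader might infer that .87 is wrong for both strata. The documents support that only at 0.025, the level that reproduces the table. At 0.05 the HIV-uninfected figure agrees with the print, but by coincidence: the table's own 0.30 row would then read .92, a figure the protocol never gives. The HIV-infected figure differs from .87 at either level.
- **The table is conditional on 0.30.** This also stands. Given 0.30 and one-sided 0.025 the table is computed correctly. The weakness is the planning input and the unstated level.
- **The HIV-specific rates also come from pregnant women.** They do, and the trial enrols non-pregnant women. Table 4 gives a postpartum rate of 16.43 per 100 person-visits, not split by HIV status. Entered as a control rate, it gives power of about .54 at 0.025 and .66 at 0.05. Printing .975 or .99 without that caveat would overstate confidence.
- **Comparing strata.** A reader might infer that the plan would treat significance in one stratum and not the other as a difference between them. Section 12.6 does not say so; it compares effects between the groups.
- **Small impact.** The tables concern a single visit with at least 375 women, and 12.6 also pools visits with generalized estimating equations. In HIV-infected women the error is conservative.

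**Conclusion.** The point holds as a mismatch between a per-stratum power statement and a mixed-HIV control rate, compounded by an alpha that does not match the table. One figure cannot serve both strata at either level. On the 0.025 basis the HIV-uninfected stratum has about 7 points less power than printed (.865 to .794) and the HIV-infected stratum about 11 points more (.865 to .975). On the 0.05 basis the HIV-uninfected stratum is at the printed value and the HIV-infected stratum about 12 points above it.

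This rests on Table 3 as the source of the 30%, on 30% BV in each cohort year, and on a 33% relative reduction in both strata. The pooled rates move by only about half a point under the alternative year split shown; the 1993-only figures are less stable. The documents do not show that the trial is too small in either stratum on these rates. Whether pregnant women are a suitable source at all is a separate and larger question for power.

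**What to change.** In Research Plan D.4 and Manual of Operations 12.4.1:

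1. State the one alpha that applies, reconciling the one-sided 0.05 of the power section with the one-sided 0.025 final test in the monitoring text.
2. In Tables 11 and 12.1, replace the single 0.30 row with two rows computed at that alpha: HIV-uninfected (about 0.26) and HIV-infected (about 0.42). For a 33% reduction these are .79 and .975 at 0.025, or .87 and .99 at 0.05. Recompute the 50% column at the same time. Inserting the 0.025 figures while leaving 0.05 in the text would create a new contradiction.
3. Rewrite the sentence that claims 0.87 power so that it gives both strata.
4. Note beside the rows that both rates are derived from pregnant women, assuming 30% BV in each cohort year, and that the postpartum rate in Table 4 is lower (16.43 per 100 person-visits).

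The cost is a few sentences and two table rows. The HIV-uninfected power becomes slightly less favourable, and no extra patients are needed.
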